### Data collection

Table 1 outlines data collection, measures, sources, and timing for each construct.

**Table 1 Tab1:** Theoretical constructs, measures, data sources, and data collection timing

Construct	Measures	Source	Timing
Implementation support	Frequency, duration, and mode of PF contacts	PF contact logs	I
	Frequency, duration, and mode of academic detailing contact	Contact, webinar logs	I
	Attendance at regional collaborative meetings	Attendance logs	I
Practice capacity for QI	Change Process Capacity Questionnaire	KI survey	B, E, F
	Adaptive Reserve Questionnaire	Provider/staff survey	B, E, F
Organizational readiness	Organizational Readiness for Change Questionnaire (ORIC)	Provider/staff survey	B
Implementation Policies and Practices (IPPs)	Key Driver Implementation Scales	PF Ratings	I
	Implementation barriers, facilitators, and IPPs	KI interview	B, E
Implementation climate	Implementation climate questionnaire	Provider/staff survey	E, F
Implementation effectiveness	ABCS measures/clinical measures	HIE	B, I, E, F
	Acceptability of implementation support	KI interview	E
Innovation effectiveness	Patient outcomes (communication, shared decision-making)	Patient survey	B, E
	Patient outcomes (healthcare utilization and mortality)	Claims data	B, E, F
	Practice outcomes (e.g., financial benefits)	KI Interview	E, F
Inner context	Practice characteristics, patient population, EMR capabilities	KI survey, PF contact logs	B, E,F
Outer context	External policies and incentives, market conditions	KI survey, KI interview, PF contact logs	B, E, F

Because readiness is conceived as an organization-level construct, we will test whether sufficient inter-rater reliability and inter-rater agreement exist to aggregate individual responses to the practice level [22–26]. If tests do not justify aggregation, we will use a measure of intra-practice variability in readiness rather than a practice-level mean in our analysis [15, 16].

Source: *PF* practice facilitator, *KI* key informant; timing: *B* baseline, *I* intervention, *E* end of intervention, *F* 6 and 12 months post-intervention

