#### Interviews

We will conduct semi-structured KI interviews (*N* = 300) at end-of-intervention and 6 months post-intervention to obtain supplemental data about organizational changes for evidence-based CVD prevention (implementation policies and practices) and influential inner and outer context events. The KI interview at end-of-intervention will also ask about acceptability of the implementation support received (implementation effectiveness). The KI interview 6 months post-intervention will ask about practice-level outcomes (innovation effectiveness).

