#### Aim 4: Evaluate the effect of practice facilitation on practice capacity to implement future evidence-based clinical guidelines

Our primary hypothesis is that primary care practice support will improve capacity to implement other evidence-based clinical guidelines in the future. Our secondary hypotheses are that (a) contextual factors will moderate the effect of primary care practice support on practice capacity to implement additional evidence-based clinical guidelines, and (b) primary care practice support will generate additional positive practice outcomes.

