#### Statistical analysis

We will analyze adaptive reserve and change process capability with a linear mixed model applied to the measures collected at baseline (*t* = s_i_), at the end of the intervention period (*t* = s_i_ + 12), and, for the early enrolled practices, at 6 months post-intervention (*t* = s_i_ + 18). The model to assess improvement in these outcomes is a simplification of model (1) because there are only two repeated outcomes:6$$ E\left({Y}_{\mathrm{i}\mathrm{t}}\Big|\ {b}_{\mathrm{i}0,}{b}_{\mathrm{i}1}\right) = {\beta}_0 + {b}_{\mathrm{i}0} + {\beta}_1{X}_{\mathrm{i}1} + {\beta}_2{X}_{\mathrm{i}2} + {\beta}_{12}{X}_{\mathrm{i}1}{X}_{\mathrm{i}2} + {g}_1\left({t}^{*};\uppsi \right) + {b}_{\mathrm{i}1}t + {\beta}_3{X}_{\mathrm{i}\mathrm{t}3}+{\beta}_4{X}_{\mathrm{i}\mathrm{t}4} $$where *X*_it3_ = 1 if *t* = s_i_ + 12 (end-of-intervention period) and *X*_it3_ = 0 otherwise; *X*_it4_ = 1 if *t* = s_i_ + 18 (6 months post-intervention) and baseline is the reference time period. Other assumptions are as in model (4). Primary interest is in *β*_3_, the difference in mean measure between baseline and end-of-intervention period.

In secondary analyses, contextual factors will be examined as additional main effects and as statistical interactions with *X*_it3_ in order to assess whether there are effect modifiers for the effect of primary care practice support on practice capacity to implement future evidence-based clinical guidelines. To test the hypothesis that primary care practice support generated additional positive practice outcomes, we will calculate 95 % confidence intervals for proportions of practices reporting positive outcomes, both overall and stratified by practice characteristics (inner context). We will also use logistic regression to ascertain whether additional positive outcomes varied as a function of primary care practice support intensity, KDIS scores, ABCS measures, and inner context variables.

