### Limitations

Recruiting and retaining a large number of practices to engage in a yearlong, comprehensive quality improvement effort poses significant challenges. Potential recruitment barriers include fear of financial risk, reluctance to share data, acquisition by larger health systems, and competing priorities. Potential retention barriers include loss of a key clinician, resignation of a practice manager, and financial difficulties. We will attempt to mitigate these barriers by using practice facilitation to help practice achieve other goals (e.g., PCMH recognition) or enhance billing for services. Also, CCNC and AHEC will leverage their strong relationships with hospitals and health systems to boost recruitment and prevent attrition.

Our stepped-wedge study design affords some control of the effects of secular trends and other factors unrelated to our comprehensive quality improvement strategy. We will supplement this by documenting and including in our statistical analysis temporal events that could affect the implementation and outcomes of the strategy. However, the effects of outer context factors can be challenging to measure and model.

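### Aim 4's causal secondary hypothesis on practice outcomes is to be tested with a one-sample confidence interval on an outcome read only after support, so it can be described but not tested

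*Protocol article*

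**What the plan says.** The Aim 4 section lists as secondary hypothesis (b) that "primary care practice support will generate additional positive practice outcomes". The Aim 4 statistical analysis takes this up as a test: "To test the hypothesis that primary care practice support generated additional positive practice outcomes", and the method it then names is "we will calculate 95 % confidence intervals for proportions of practices reporting positive outcomes, both overall and stratified by practice characteristics". It gives no null value, reference proportion or before-after contrast. A second analysis follows: "logistic regression to ascertain whether additional positive outcomes varied as a function of primary care practice support intensity", with KDIS scores, ABCS measures and inner-context variables as further predictors.

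On timing, Table 1 lists "Practice outcomes (e.g., financial benefits") from the key-informant interview at E and F only, where the footnote defines these as "end of intervention, *F* 6 and 12 months post-intervention". The Interviews section says: "The KI interview 6 months post-intervention will ask about practice-level outcomes (innovation effectiveness"). The two places differ on whether the end-of-intervention interview also covers these outcomes. Neither includes baseline.

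On content, the Measures section describes a qualitative item. The informant is asked whether CVD prevention brought better pay-for-performance standing, certification credits, quality-program payments or greater appeal to shared-savings programs.

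**The concern.** The hypothesis says that support caused something, but the planned quantity is the proportion of supported practices that report it. Without a reading under the control condition, that proportion mixes what support added with what the same informants would have reported anyway. The item adds two difficulties. The informant makes the attribution, and the Research design section says participating practices are not blinded. The item also credits CVD prevention, whereas the hypothesis credits practice support.

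At stake is one secondary conclusion. If the text is followed as written, the trial could report that support generated financial or recognition benefits on evidence that cannot carry that statement.

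**Working it through.** **1. Practices available.** The Interviews section plans 300 key-informant interviews. The Aim 4 power section allows 15% dropout: 300 × (1 − 0.15) = 255, which reproduces its figure. That figure is stated for the primary hypotheses. No number is given for this hypothesis, so both 255 and 300 are used below.

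**2. What is observed.** Let p be the proportion reporting a positive outcome after support, q the proportion of the same practices that would have reported one without support, and d the part due to support. Then p = q + d. The hypothesis concerns d. The schedule yields p only, and the article gives no value for q.

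**3. Illustration (q is an assumption throughout).** Exact (Clopper-Pearson) 95% intervals:

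| Reports | Proportion | 95% interval |
|---|---|---|
| 26 of 255 | 10.2% | 6.8% to 14.6% |
| 51 of 255 | 20.0% | 15.3% to 25.4% |
| 60 of 300 | 20.0% | 15.6% to 25.0% |

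Take the second row and subtract an assumed q:

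| Assumed q | d = 20.0% − q |
|---|---|
| 0% | 20 points |
| 5% | 15 points |
| 10% | 10 points |
| 20% | 0 points |

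The interval is the same in all four cases. More practices would narrow it but would not separate d from q.

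**4. The logistic regression.** By the Research design section every practice receives the intervention, so this regression has no unexposed group. Intensity is not randomized. It is defined as the share of contacts made in person, and facilitation hours depend on readiness at enrollment. KDIS scores are rated during the intervention. The regression describes which supported practices report more. It does not estimate q.

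**5. The other Aim 4 outcomes.** Table 1 schedules adaptive reserve and change process capacity at baseline, end of intervention and follow-up. Model (6) analyses them against baseline with a calendar-time term. The missing baseline therefore concerns practice outcomes only.

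**6. What a baseline reading could support.** Starts fall at months 9, 11, 12, 14 and 16. Adding 12 gives end readings at months 21, 23, 24, 26 and 28. If baseline items are read at the start, the two sets (9 to 16 and 21 to 28) do not overlap, so adjustment for calendar time depends on the assumed shape of the trend. Model (6) accepts the same limit for its own outcomes. Its random intercept and slope should not be carried over to a binary item, however. Two binary readings per practice give four response patterns, or three free probabilities per covariate pattern, against two variances, one covariance and the fixed effects.

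**The case against.** The strongest defence is that the item asks for attributed improvement. A gain that would have come anyway counts only if the informant credits CVD prevention with it. This stands in part. A reader might infer that any background rate of gains would pass as an effect, but the documents do not support that. In the notation above, q is the rate of attributed reports without support, which may be well below the rate of gains of any kind. It is still unknown, and an unblinded informant's attribution does not replace a comparison.

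A reader might also infer that a positive conclusion is close to automatic, since a single report among 300 gives an exact interval of 0.008% to 1.84%, which lies above zero. The article fixes no such decision rule. A very low interval could equally be reported as showing almost no benefit, and a benchmark value could sit in an analysis plan that is not shown. What the article does fix is the schedule without a baseline and the use of the interval as a test.

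A third tempting reading is that facilitator help contaminates the outcome. The Limitations section speaks of "using practice facilitation to help practice achieve other goals (e.g., PCMH recognition) or enhance billing for services". That help is delivered through facilitation and so is arguably part of the support under test. Neither PCMH recognition nor billing is among the outcomes listed in the Measures section.

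Finally, this is a secondary hypothesis of the fourth aim with a qualitatively measured outcome. That stands and limits the weight of the point.

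**Conclusion.** The concern holds in a limited form. The stated test cannot support the stated causal conclusion, because the outcome has no control-period reading and the interval has no comparator. The logistic regression does not repair this. The size of any resulting error cannot be computed, because the article gives no rate of positive reports without support. Over assumed rates of 0% to 20%, an observed 20% fits a support effect anywhere from 20 points down to none. The proportion with its interval remains a valid description of what supported practices report. The primary Aim 4 analysis is unaffected, and the severity is minor.

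**What to change.** **Preferred.** Reword the sentence in the Aim 4 statistical analysis so that it no longer announces a test of what support generated. State that the proportion of practices reporting outcomes they attribute to CVD prevention will be described with a 95% confidence interval, overall and by inner context. State that the logistic regression explores variation among supported practices, and that no causal conclusion will be drawn from either. This costs a few sentences. In the same edit, reconcile Table 1 with the Interviews section on when practice outcomes are asked.

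**Alternative, if a causal statement is wanted.** Where baseline key-informant surveys are still open, add factual items without attribution, such as certification credits, program payments and pay-for-performance standing over the past 12 months. Repeat them in the end-of-intervention survey. Analyse the within-practice change with a random-intercept logistic model or GEE, adjusted for strata and calendar time, and say that the calendar-time adjustment rests on the assumed trend. The cost is a slightly longer survey given twice and one further model. The Trial status section says that practices are being recruited and that the first starts are in January 2016. It does not say how many baseline surveys are already complete, so the sponsor should check this before choosing the alternative.

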### Statistical power

For the primary hypotheses, we conservatively calculate power by ignoring any information from individuals 6 months post-intervention and allow a 15 % dropout (*N* = 255). Additional file 4 shows that our minimal detectable differences are similar to mean change reported by Nutting et al. and Solberg et al., respectively, for adaptive reserve and CPCQ [10, 11].

#### Supplemental analysis

We will explore the reasons why some practices benefited more than others by identifying themes about actions taken, missed opportunities, influential inner and outer contextual factors, and other situational factors.

#### Trial status

Practices are being recruited. The high-readiness practices randomized to start in month 9 will receive the intervention beginning January 2016.

## Discussion

### Significance

Practice facilitation, when combined with other quality improvement interventions, is an effective strategy for supporting the implementation of evidence-based guidelines in primary care settings [21]. However, no previous effort has conducted a controlled trial of practice facilitation at the scale or level of intensity that we propose. Results will have significant implications for healthcare payers, government agencies, and other stakeholders seeking to use practice facilitation, alone or combined with other quality improvement interventions, to support national initiatives to scale up and spread evidence-based clinical guidelines.

### Limitations

Recruiting and retaining a large number of practices to engage in a yearlong, comprehensive quality improvement effort poses significant challenges. Potential recruitment barriers include fear of financial risk, reluctance to share data, acquisition by larger health systems, and competing priorities. Potential retention barriers include loss of a key clinician, resignation of a practice manager, and financial difficulties. We will attempt to mitigate these barriers by using practice facilitation to help practice achieve other goals (e.g., PCMH recognition) or enhance billing for services. Also, CCNC and AHEC will leverage their strong relationships with hospitals and health systems to boost recruitment and prevent attrition.

Our stepped-wedge study design affords some control of the effects of secular trends and other factors unrelated to our comprehensive quality improvement strategy. We will supplement this by documenting and including in our statistical analysis temporal events that could affect the implementation and outcomes of the strategy. However, the effects of outer context factors can be challenging to measure and model.

#### Impact

If successful, our comprehensive quality improvement strategy will have a positive impact on both practices and patients. Hundreds of small- to medium-sized primary care practices, many located in rural and medically underserved areas, will be better prepared for the transition to value-based payment, wherein an increasing proportion of reimbursement is tied to performance on quality of care measures. Likewise, discernible reductions in cardiovascular risk among the estimated 900,000 adult patients served by participating practices would likely prevent thousands of cardiovascular events within 10 years.
